## Abstract

Inadequate intake of fruits and vegetables (FV) and moderate-to-vigorous physical activity (MVPA) in children has become a global public health problem. Therefore, school-based gardening and cooking (SGC) and sports participation (SP) interventions may be effective in improving children’s FV intake and MVPA. The aim of this study is to develop and evaluate the effectiveness of SGC and SP interventions on FV intake and MVPA among Chinese children. In this cluster randomized controlled trial study, 237 children in grades 4–5 from six public primary schools from Changsha, Hunan Province, China will be randomly assigned to: (1) a SGC and SP combined intervention group; (2) a SP intervention group; (3) a regular practice group. The intervention clusters will be implemented for a period of 6 months and follow up will be carried out after 12 months. The outcome will be collected using a combination of self-reported and objective measures. Primary outcomes will include children’s FV intake and duration of MVPA per day, and secondary outcomes will included frequency and attitudes of FV intake and SP, in addition to other measures. Finally, a process evaluation will be used to analyze the facilitators and barriers to intervention implementation. Trial Registration: (Registration Number: ChiCTR2200064141).

## 1. Introduction

An inadequate intake of fruits and vegetables (FV) and insufficient physical activity (PA) among children have become global health concerns [1,2,3]. Inadequate intake of FV in children not only leads to deficiencies in vitamins, minerals and dietary fiber, which are essential to human health [4,5], but it also increases the risk of many chronic non-communicable diseases in adulthood, such as obesity, diabetes, cardiovascular disease, cancer, etc. [6,7,8,9]. Additionally, insufficient moderate to vigorous physical activity (MVPA) is associated with an increased risk of obesity, metabolic syndrome and mental health problems in children [10,11,12].

Although many studies have shown that dietary and PA interventions can improve FV intake and MVPA in children [13,14], and in particular that multifaceted interventions using both diet and sports participation (SP) are more effective than diet or SP interventions alone in improving children’s health [15,16,17], there is still a lack of sustainable and structured intervention programs. Most of the current diet and SP program for children in China have been designed with the specific goal of improving obesity, neglecting the development of lifestyle-related interventions such as improving children’s eating and PA behavior [18,19,20]. However, the development of good lifestyles during childhood is important in promoting health and preventing disease [21,22]. In recent years, there has been increasing interest in the application of intervention programs for school gardening and cooking (SGC) activities combined with SP to improve children’s eating and PA behavior [16,23,24].

SGC activities is a school-based nutrition intervention project; by planting and cooking FV in schools, students can receive nutrition knowledge under the guidance of teachers and experience the process of planting and cooking FV [25]. SP is a subset of PA and youth sport has been defined as a program that provides a systematic sequence of practices and contests for children and youth [26]. Many studies show that SGC activities are effective in improving children’s FV intake nowadays [27,28,29], and that different forms of SP can have a significant effect on improving children’s MVPA (especially sports that are both fun and challenging to ensure adherence to the intervention) [30,31,32,33]. However, research in this area is still very limited in China. For children, most of their waking hours is spent at school, making it the best environment for implementing SGC activities and SP interventions [34]. In China, the *Curriculum Program and Curriculum Standards for Compulsory Education (2022 Edition)*, published by the Ministry of Education in 2022, further optimizes the curriculum, such as the complete separation of labor from the former integrated practical activities curriculum and the publication of *the Compulsory Education Labour Curriculum Standards (2022 Edition).* Schools are required to organize students to participate in daily life work, productive work and service work in a planned manner, with an average of no less than one lesson per week. The focus is on requiring primary school students in grades three to four to experience FV growing and to learn to prepare FV salad, while primary school students in grades five to six are expected to grow common local FV trees and to learn to cook two to three home-cooked dishes. In addition, the *Physical Education and Health Curriculum Standards for Compulsory Education (2022 Edition)* shows that the percentage of “Physical Education and Health” has increased to 10–11%, making it the third most important subject, and requires the integration of new sports such as fancy jumping rope into the teaching content. Therefore, implementing a structured school-based intervention program for children based on SGC and SP aligns with curriculum requirements in China.

A recent study used the multifaceted intervention effectively reduced the mean BMI and obesity prevalence in primary school children across socioeconomically distinct regions in China [35], but it did not change MVPA, physical fitness, and other outcomes. This is mainly due to the fact that the researchers did not use sport participation interventions that were fun and challenging. Instead, students are required to do PA for a total of one hour per day, which does not allow for a good level of intensity and duration of PA for children. Therefore, the choice of a sensible intervention is crucial. Based on the latest education policy in China, a physical and nutritional health promotion program for primary school children in grades four to six will be developed using a combined SGC and SP intervention to increase the intake of FV and the duration of MVPA among school children aged nine to twelve years, and to improve their FV intake and SP frequency, attitude and preference, with the following specific objectives: (1) to develop a program that included sports participation in the existing SGC intervention program for primary school children in China; (2) and to explore the effects of SGC and SP on the intake of FV, intake motivation, time and frequency of MVPA, and other healthy conditions among school children in China. 

### 2.2. Recruitment

#### 2.2.1. Recruitment of the Schools

Considering the limited cognitive ability of grade three school-age children who cannot guarantee accurate completion of self-reporting and the fact that grade six school-age children will soon move on to junior high school and have limited time at school, which may have some impact on subsequent follow-up, we have chosen grade four to five school-age children as the target group for recruitment, not only so that they have good receptivity to educational information but also so that they have sufficient time to complete the intervention and follow up. The schools will be randomly selected if they meet the criteria described below:

Inclusion criteria: Schools will be included if they were public primary schools and with a minimum of 300 primary students. The school principal agrees to the randomization process and comply with this study protocol.

Exclusion criteria: Schools will be excluded if they are boarding schools and schools for special populations, as are schools with fewer than two classes in grades four to five or schools with plans to cease operating within a year, and schools without established gardens or sufficient space to plan garden construction, or receiving other similar interventions will be excluded.

#### 2.2.2. Recruitment of the School Children

Informed consent forms will be provided to all students and their primary caregivers after school recruitment is completed and before the baseline survey begin. A questionnaire on the student’s health status will be distributed to each student and primary caregiver after they had both signed informed consents. The project staff will collect the questionnaires and if a parent reports one of the following conditions, his or her children will be excluded: (1) hypertension, medical history of heart disease, asthma, diabetes, tuberculosis, hepatitis, or nephritis; (2) obesity caused by side effects of drugs or endocrine diseases; (3) abnormal physical development such as gigantism or dwarfism; (4) physical deformity such as severe scoliosis, limp, pectus carinatum, obvious X-leg or O-leg; (5) unable to participate in moderate to vigorous physical activity; (6) unable to understand the information in the questionnaire. Ultimately, we will recruit 96 primary school students in grades 4–5 in each school. If the total number of students in two classes is not 96, we will randomly select a small number of students from grade three until the sample size is reached.

### 2.3. Sample Size Estimation

With PA duration rate (PA duration > 60 min per day) and FV intake rate (FV intake >700 g per day) as a calculated basis: control group weekly PA and FV intake rate divided into p1 = 20.6% and p1 = 23.1%, it is expected that after the intervention the daily PA hours and FV intake of the intervention group is 50% of the standard, other control groups are not considered for the time being, an alpha of 0.05, power of 90% and 20% of lost visits are considered, the final settlement results: 79 people in each group, a total of 237 people.

### 2.4. Randomisation Procedures

Schools located in six different regions (clusters) will be randomly assigned to the combined intervention group, the single intervention group or the control group using a computer-generated random number system (simple random sampling method) in a 1:1:1 ratio. Randomization will be carried out by an independent staff member from the Department of Nutrition and Food Hygiene, School of Public Health, CSU. To ensure allocation concealment, randomization will not be carried out until after the baseline survey has been completed. Blinding of the school allocation in this setting will not be possible. Therefore, the investigators and data collectors will not be blinded in this trial. However, the outcome assessors and the data analysts will be blinded.

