### 2.8. Outcome Evaluation

The outcome indicator measure will be administered at three points in time. Firstly, a baseline measurement will be taken prior to randomization to a group of six public primary schools. Then the same measurement will be taken after the completion of the six-month intervention, and a final identical measurement will be taken six months after the completion of the formal intervention period to assess the sustainability of the intervention (6 months after completion of the formal intervention period, as recommended by the National Obesity Observatory). Data collection will be completed by trained data collection workers using paper questionnaires, exercise bracelets, height boards, scales and tape measures for students, and electronic questionnaires and interview guides for parents using those already entered into Questionnaire Star. The specific measurement information is shown in Table 2.

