**PA and other behavioral conditions**					
PA frequency and attitudes of children.	√	√		6 to 17-year-old Chinese children physical activity questionnaire, CCPAQ (The CCPAQ is a valid (R = 0.78) and trustworthy (intraclass correlation coefficient = 0.70) device for measuring PA)	Students should finish the questionnaires in the classroom in the presence of the trained outcome assessors, who can provide guidance and help.
Daily Screen time	√	√		6 to 17-year-old Chinese children physical activity questionnaire, CCPAQ (The CCPAQ is a valid (R = 0.78) and trustworthy (intraclass correlation coefficient = 0.70) device for measuring PA)	Students should finish the questionnaires in the classroom in the presence of the trained outcome assessors, who can provide guidance and help.

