**Dietary behavior**					
Daily intake of FV and food intake frequency	√	√		The Food Frequency Questionnaires, FFQ required for the study was developed using the food frequency questionnaire compiled by the 2016 Chinese Resident Dietary Survey with appropriate adjustments according to the study content and purposes of the study, with Cronbach’s > 0.7.	The questionnaires should be self-reported by parents or other primary caregivers of the students.
Children’s FV preferences, identification and the attitude and willingness to eat FV	√	√		Using the Dutch Eating Behavior Questionnaire child-version, DEBQ-C.Zhao Yan et al.developed the Chinese version of the children’s dietary behavior scale according to the English version of DEBQ-C, with Cronbach’s > 0.7	Students should finish the questionnaires in the classroom in the presence of the trained outcome assessors, who can provide guidance and help.
Parental attitudes towards children’s FV intake and SP	√	√		The questionnaire will be adapted from the nutrition knowledge, attitude and praxis questionnaire (KAP) to evaluate children’s knowledge, attitudes and praxis about FV, with Cronbach’s> 0.7.	Students should finish the questionnaires in the classroom in the presence of the trained outcome assessors, who can provide guidance and help.
**Questions and recommendations on the implementation of the interventions**		√		Interview questions included school climate and barriers to implementation of interventions, perceived benefits and challenges to intervention, opinions and perceptions about the intervention’s effects on student involvement, behaviorand class-related outcomes, beliefs about parental involvement, potential for sustainability, overall recommendations to other school principals and ideas for improvements.	The questionnaires should be filled by the trained investigators after face-to-face interviews with school principals, teachers and volunteers.

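### Section 2.4 claims blinded outcome assessors, but Section 2.8 and Table 2 give the same classroom questionnaires to an unblinded and a blinded role, and the claim cannot protect caregiver-reported fruit and vegetable intake

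*Protocol article*

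**What the plan says.** Section 2.4 (Randomisation Procedures) makes three statements in sequence. On the schools: "Blinding of the school allocation in this setting will not be possible". On staff, as a consequence: "the investigators and data collectors will not be blinded in this trial". Then the exception: "However, the outcome assessors and the data analysts will be blinded".

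Section 2.8 (Outcome Evaluation) says who handles the children's measurements: "Data collection will be completed by trained data collection workers using paper questionnaires, exercise bracelets, height boards, scales and tape measures for students". Parents use electronic questionnaires and interview guides.

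Table 2 describes the children's questionnaires differently: "Students should finish the questionnaires in the classroom in the presence of the trained outcome assessors, who can provide guidance and help". The same method is given for PA frequency and attitudes, screen time, and FV preferences and attitudes. It is also given for the questionnaire on parental attitudes. For FV intake, a primary outcome, Table 2 says: "The questionnaires should be self-reported by parents or other primary caregivers of the students".

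Table 1 names primary caregivers as a target of the cooking and home gardening components, which only the combined arm receives. They are also a target of the exercise health theory sessions.

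**The concern.** Blinded outcome assessment is a safeguard that readers use to judge subjective outcomes. Here it is stated without qualification, while the article's own account of data collection does not bear it out.

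Two things are at stake. First, for the classroom questionnaires it is unclear whether the people helping children to answer are the blinded or the unblinded staff. Randomisation is by school, so anyone who learns what one school has been doing knows the arm of every child in it. Second, for FV intake the reporter is the caregiver, and no blinded staff member stands between that person and the recorded value. Caregivers in the combined arm take part in FV activities, and those in the other two arms do not. Any reporting influenced by participation would therefore differ by arm and would tend to favour the combined intervention. A general statement that assessors were blinded would lend this outcome a protection it does not have.

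**Working it through.** The point depends on no sample size, rate or power figure, so there is nothing to compute. The check sets the relevant sections side by side, taking the data collection workers of Section 2.8 to be the data collectors of Section 2.4.

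**Step 1: who handles the children's questionnaires?**

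| Place | Role named | Status under Section 2.4 |
|---|---|---|
| Section 2.8 | Data collection workers | Unblinded |
| Table 2 | Trained outcome assessors, present and helping | Blinded |

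If these are the same people, Section 2.4 contradicts itself. If they are different people, the assessors work in the classroom on the same task as unblinded colleagues. They are also inside a school whose allocation Section 2.4 says cannot be masked, and the article describes nothing that keeps the arm from them.

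**Step 2: what does assessor blinding protect, outcome by outcome?**

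- *FV intake (primary).* The caregiver reports it on a food frequency questionnaire, so assessor blinding gives no protection.
- *Daily MVPA (primary).* It is read from a wrist band as a one-week average. What protection there is comes from the device.
- *Child questionnaires (secondary).* They are completed with help from staff whose blinding status is contradictory (Step 1).
- *Height, weight, waistline (secondary).* Section 2.8 gives these to the data collection workers, openly unblinded. There is no contradiction here, but no blinded assessor either.

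The article describes no outcome as measured by someone who could be shown to be blinded.

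**Step 3: does caregiver involvement in FV activities differ by arm?**

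- Combined arm: caregivers are targets of cooking and home gardening (Table 1).
- SP arm: caregivers are listed only for exercise health theory (Table 1).
- Regular practice: no intervention component (Section 2.6.3).

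It does differ, so differential reporting of FV intake is plausible.

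**Step 4: are deliverers and collectors kept apart?** Table 1 says teachers deliver sessions and that their training covers part of the data collection. It does not say which data. The article states no separation.

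**Step 5: which time points?** Baseline precedes randomisation (Sections 2.4 and 2.8) and is unaffected. Table 2 marks FV intake and the child questionnaires at baseline and 6 months only, so the exposed measurement is the one at 6 months.

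**The case against.** A reader might infer that no assessor could possibly be blind. The documents do not show that. Section 2.2.1 excludes schools with neither a garden nor room for one, so control schools may already have gardens. The Introduction says the national curriculum asks for FV growing, salad preparation and fancy rope skipping. Section 2.6.2 says Changsha schools must provide an hour of exercise a day and that rope skipping is an entrance exam item. Follow-up measurement comes after the six-month intervention ends, so an assessor need not see a session. These cues to allocation are weak, and a fuller protocol might describe safeguards. This stands: unblinding through children or teachers is likely, but impossibility is not shown.

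A reader might also take the whole quoted sentence to be false. It is not: nothing contradicts the blinding of the data analysts.

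Nor does Section 2.4 claim that caregivers are blinded, and the Discussion already concedes that self-reported FV intake is open to bias. That also stands. However, the Discussion does not connect this bias to allocation or to the caregivers' part in the intervention, and it leaves the assessor-blinding statement unqualified.

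Finally, a reader might want to attach a size by assuming a percentage of over-reporting and a standard deviation of intake. The article gives neither, so such a figure would only restate its assumptions.

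None of these objections removes the conflict between Section 2.4, Section 2.8 and Table 2. No unseen document could make caregiver-reported intake a blinded outcome while that method of reporting is kept.

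**Conclusion.** The concern holds in a limited form. As written, assessor blinding is a stated property that the described procedures do not deliver. The classroom questionnaires are assigned both to an unblinded and to a supposedly blinded role, and the FV primary outcome is reported by caregivers whose involvement in FV activities differs by arm. The finding covers questionnaire outcomes after randomisation, at 6 months in Table 2. It does not extend to the analysts or to baseline, and it touches band-measured MVPA much less.

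No magnitude can be derived from the documents. The likely direction, in favour of the combined arm for FV intake, is a judgement based on Table 1. The conclusion assumes that data collectors and data collection workers are one role. If they are not, the article still leaves unexplained how assessors in the classroom are kept unaware of allocation.

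**What to change.** 1. Reconcile the roles in Section 2.4, Section 2.8 and Table 2, so that each measurement has one named role with one blinding status.
2. In Section 2.4, limit the blinding statement to the data analysts, working with coded arm labels.
3. Describe FV intake and all questionnaire outcomes as unblinded reports. Link the self-report limitation in the Discussion to allocation, and word the FV conclusion to match. Note that band-measured MVPA is the primary outcome less dependent on an unblinded reporter.
4. Within existing staff, do not let those who deliver sessions at a school collect outcomes there, and limit classroom help to explaining the wording of questions.

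Items 1 to 3 are changes of text, and their price is a less favourable blinding statement. Item 4 needs some reassignment of staff and a small change in procedure. The article gives no staff numbers, so how far the separation can go has to be judged by the sponsor.

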### 2.5. Intervention Selection and Theoretical Basis

The SGC and SP courses are adapted from the *Junior Master Gardener Health and Nutrition* from the *Garden and the Walk Across Texas programs*, respectively. The program was developed by Texas A&M AgriLife Extension Service and has a well-established curriculum [37]. This academic year intervention is based on social cognitive theory [38], as shown in Figure 2, with the primary goal of engaging students at school and at home to promote behavioral change in diet and PA through personal and environmental influences. All programs will then be adjusted and modified based on pre-experimental results and focus group discussions.

To fill the research gap, the intervention was developed in four stages in line with the new policy on school education in China. (1) We have systematically reviewed the previous literature to identify measures relevant to the form and effectiveness of this intervention [24]. (2) Focus group discussions and interviews will be conducted with key informants (children, parents, teachers, head teachers, local health and education officials) to further revise and refine the intervention program. (3) We will conduct a 3-month pilot study with 90 grades 4 students (mean age: 9.38 ± 0.62 years) in a primary school in Changsha to test the feasibility of the initial proposed intervention. (4) After many rounds of discussions with nutrition experts, sports and health experts, school leaders and teachers, we will adapt the curriculum to suit the teaching of Chinese primary school students.

